### Trial design

The “Healthy Change” study is a multicenter two-arm randomized trial with four research sites, three in Mexico: a) Nuevo León, b) Tamaulipas, and c) Zacatecas, and one in San Antonio, Texas, USA. At each site, two childcare centers are randomly assigned to either the intervention or the attention control group. A total of 360 pairs of preschoolers and their mothers, i.e., 90 pairs per site, are recruited for the trial. Intervention participants will receive a four-weekly group education focusing on maternal perception of children’s bodyweight that facilitate healthy behavioral changes for the family. Control participants will receive a four-session group education on food hygiene and first aids as attention control. The outcomes include change in the proportion of mothers who accurately estimate their children’s weight categories, change in feeding style, maternal self-efficacy and actions taken in managing the child’s excessive weight gain. Data are to be collected at baseline and the end of the four-week group education from both groups. The study began on 08–29-2015, and will end on 11–20-2018.

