### Sample size and statistical power

The primary outcome of this intervention will be the proportion of mothers who adequately estimate their child’s weight status. Assuming the intra-class correlation coefficient (ICC) of 0.03, to detect a change of mother’s accurate estimation of children’s weight status from 50 to 70% with 80% power, 37 mother-child pairs would be required per research center per arm [23]. Accounting for a 15% attrition rate, each research site will enroll 45 pairs of mothers and children for the intervention and another 45 pairs for the control group. The total sample size for this four-center trial will be 360 pairs of mothers and children.

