#### Outcome evaluation

Baseline and post-intervention data will be collected on all participants. Each mother will receive 25 USD at the end of the intervention for their participation in the data collection. The primary outcome of this study is the proportion of mothers who accurately estimate their children’s weight status. Maternal perception of child’s weight is measured using the Parents’ Perceptions about Their Child’s Appearance and Health Questionnaire [19]. Mothers are asked to indicate their child’s weight status from 5 response options: “underweight”, “a little underweight”, “about the right weight”, “a little overweight”, or “overweight” (MPCW by words). Mothers also checked one of the body sketches (MPCW by image) in the age range 2 to 5 years old [19, 26].

Secondary outcomes include:Change in the maternal feeding styles. Maternal feeding styles is measured using the Caregiver Feeding Style Questionnaire. The questionnaire consists of 19 questions grouped in two dimensions: demandingness and responsiveness. Subsequent calculation of the median of both dimensions places participants in one of the four styles, i.e., authoritative, authoritarian, indulgent, or uninvolved [16].Increased self-efficacy score of maternal influencing on children’s health behavior. Mothers rate their confidence on a 5-point Likert scale ranging from “strongly disagree” to “strongly agree” on these two statements: “I can influence my child’s food choices” and “I can influence my child’s amount physical activity” [27].Improved score of family nutrition and physical activity. The Family and Nutrition and Physical Activity (FNPA) screening tool is used to assess mothers’ practices that may predispose children to becoming overweight [28]. The FNPA tool consists of 20 questions assessing family meals, family eating practice, food and beverage choices, material feeding restriction/ reward practice, child’s screen and activity time, sleep schedule, family activity routine and healthy environment [28]. Each question has four options: i.e., “Never/Almost Never”, “Sometimes”, “Often”, and “Very Often/Always” [28].Reduction or maintenance of the child’s BMI and BFP: The child’s weight is measured by Seca Scale 813 and height by Seca stadiometer 214, the BFP is measured by bioelectrical impedance by InBody 230.

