#### Healthy change intervention effect

The quantitative data will be analyzed in Statistical Package for the Social Sciences (SPSS) version 23. WHO Anthro (version 3.2.2, January 2011) and macros will be used to calculate children’s age- and gender- specific BMI percentile and children will be classified by the World Health Organization | BMI-for-age chart: malnutrition (percentile < 3), low weight (≥3 and < 15), normal weight (≥15 and < 85), OW (≥85 but < 97), and OB (≥97) [31]. The rate at which mothers accurately classify their children’s weight status will be calculated in two ways, i.e., by words or by images. Accurate MPCW by words will be defined as show in Table 2.

**Table 2 Tab2:** Accurate MPCW by words

Children’s actual weight status by BMI percentile	MPCW by words
Malnutrition (< 3 percentile) Low weight (≥ 3 and < 15 percentile)	“underweight” or “a little underweight”
Normal weight (≥ 15 and < 85 percentile),	“Normal weight”
Overweight (≥ 85 but < 97 percentile)	“A little overweight”
Obese (≥ 97)	“Overweight”

With regard to the MPCW by image test, an accurate perception is defined when mothers of underweight and normal weight children select an image smaller than the average image or when mothers of children with OW-OB select the average or a larger image.

McNemar’s Test will be used to test the primary outcome measure, i.e., intervention effect on change in proportion of mother’s accurate recognition of their preschooler’s weight status. The GLM Univariate procedure will be used to determine intervention effects on secondary outcomes e.g., scores of mother’s self-efficacy, feeding practices and children’s BMI percentiles and fat%. The models will include the secondary outcome measures as the dependent variables, treatment condition (intervention versus control) as the fixed factor, and confounding factors (e.g., mother’s education level, children’s gender and age) as covariates. Sub-analyses will be performed to compare intervention effects on both primary and secondary outcomes between the samples from Mexico and Texas, USA.

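### Child BMI is to be modelled linearly as a percentile, a bounded scale that compresses change in overweight children and nearly removes it in clearly obese ones; the BMI-for-age z-score avoids this

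*Protocol article*

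**What the plan says.** Three parts of the protocol article bear on this.

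- **Outcome evaluation** lists, last among the secondary outcomes, "Reduction or maintenance of the child’s BMI and BFP" (body fat percentage). It names neither a percentile nor a z-score.
- **Healthy change intervention effect** states that WHO software and "macros will be used to calculate children’s age- and gender- specific BMI percentile". It uses these values to classify weight status, with the upper bands given as "OW (≥85 but < 97), and OB (≥97".
- **The same section** then says: "The GLM Univariate procedure will be used to determine intervention effects on secondary outcomes". Its examples include "children’s BMI percentiles and fat" percentage. On the form of the model it says: "The models will include the secondary outcome measures as the dependent variables, treatment condition (intervention versus control) as the fixed factor". The covariates given as examples are the mother's education and the child's gender and age. Neither a baseline value nor a transformation is mentioned.

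On timing, **Trial design** says: "Data are to be collected at baseline and the end of the four-week group education from both groups".

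**The concern.** A percentile is a sound basis for classifying a child but a poor continuous outcome for a linear model. It cannot exceed 100, and by the protocol's own cut-off every obese child lies within the top three points. Near the median, a small change in BMI moves a child many points; in the upper tail the same change on the standardised scale moves the child very little. The fitted treatment effect is an average of percentile points, so it is driven mainly by children of ordinary weight.

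If any short-term benefit falls mostly on heavier children, the analysis is least sensitive where that benefit lies. A null result could then reflect the scale rather than the programme. The Discussion intends the results to support funding for a larger trial, so this would matter to how the BMI result is read.

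The outcome section and the analysis section also do not name the same measure: BMI in one, BMI percentile in the other.

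**Working it through.** **Is there a figure of the plan to reproduce?** No. The protocol gives no expected effect, standard deviation or baseline distribution for child BMI on any scale. Its one sample-size calculation concerns maternal perception and does not enter here.

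**Step 1: the scale.** On a growth reference, percentile = 100 × Φ(z), with Φ the standard normal distribution function. The 85th percentile is z = 1.04 and the 97th is z = 1.88. A fall of d in z, starting from z, is a fall of 100 × [Φ(z) − Φ(z − d)] percentile points. The size d = 0.2 is an assumption for illustration.

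| Start | 100·Φ(z) | 100·Φ(z − 0.2) | Fall, points | Relative to median |
|---|---|---|---|---|
| Median, z = 0 | 50.00 | 42.07 | 7.9 | 100% |
| 85th, z = 1.04 | 85.08 | 79.95 | 5.1 | 65% |
| z = 1.5 | 93.32 | 90.32 | 3.0 | 38% |
| 97th, z = 1.88 | 96.99 | 95.35 | 1.6 | 21% |
| z = 2.5 | 99.38 | 98.93 | 0.45 | 6% |
| z = 3 | 99.87 | 99.74 | 0.12 | 1.5% |

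On the z-scale each row is a fall of 0.20. Across the overweight band the percentile keeps 65% down to 21% of the response at the median. Well inside the obese band it keeps 6% or less.

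**Step 2: what this does to the linear model.** The local slope of percentile on z, relative to the median, is exp(−z²/2): 0.585 at the 85th percentile and 0.17 at the 97th. Random fluctuation is compressed by the same factor as the effect. So if the effect is the same in z for everyone, signal and noise shrink together and the loss is modest. If the effect sits only in heavier children, their signal shrinks while the noise from the other children stays at full size, and the loss is large.

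**Step 3: size of the loss (illustration).** Inputs:

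- From the protocol: 4 sites × 45 = 180 pairs per arm, and 15% attrition, giving 180 × 0.85 = 153 per arm.
- Assumed: normal baseline z, SD of change 0.3 z, two-sided 5% test, no clustering.
- Scenario A (assumed): baseline mean 0.5, SD 1.1; effect −0.25 z only in children above the 85th percentile.
- Scenario B (assumed): baseline mean 0.7, SD 1.2; effect −0.1 z in every child.

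| Scenario and model | Power, z-score | Power, percentile |
|---|---|---|
| A, baseline as covariate | about 58% | about 19% |
| B, baseline as covariate | about 81% | about 69% |
| A, post-intervention value only | about 10% | about 7% |
| B, post-intervention value only | about 11% | about 10% |

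Repeat runs with baseline as covariate gave 57–61% against 19–20% for A and 81–84% against 69–72% for B. Change scores gave the same pattern as baseline adjustment. If the effect confined to heavier children is only −0.1 z (baseline as in A), baseline-adjusted power is about 15% against 7–8%, so neither scale is informative.

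**The case against.** Several points on the other side limit the matter, and most of them stand.

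- **The power contrast needs a baseline value.** The named covariates do not include one. The list is only of examples, so baseline may be intended, but it is not stated. On post-intervention values alone, changing scale gains little. This stands, and it is why the fix includes the baseline z-score.
- **The favourable scenario is assumed.** Nothing in the protocol supports −0.25 z confined to heavier children after four weeks. Under a uniform effect the gap is about 12 points (81 − 69). Clustering is also ignored, although whole childcare centers are randomised and the protocol itself is "Assuming the intra-class correlation coefficient (ICC) of 0.03". Allowing for it would lower power on both scales. These points stand.
- **The outcome is peripheral.** Child BMI appears neither in the three objectives nor among the outcomes listed in the Abstract and Trial design. Fat percentage is analysed alongside it and is not on a percentile scale. This stands and keeps the point minor.
- **Percentile is only an example in a condensed article.** A fuller plan may settle the scale. Even so, percentile is the measure the article names for the model, and nothing in the text suggests another.

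A reader might infer that change in overweight children is all but erased. It is not: they keep roughly a fifth to two thirds of the response at the median. A reader might also infer that the programme is meant for obese children and so measures the wrong group. The eligibility section sets no weight criterion, the stated purpose is prevention, and the outcome includes maintenance as well as reduction.

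None of this shows that the percentile is an adequate linear outcome, or that the z-score has a drawback.

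**Conclusion.** The concern holds in a limited form. The protocol names BMI percentile as the dependent variable of a linear model. That scale compresses change in overweight children (5.1 points at the 85th percentile and 1.6 at the 97th, against 7.9 at the median, for a 0.2 z fall) and nearly removes it in clearly obese children (0.45 at z = 2.5, 0.12 at z = 3). This arithmetic rests only on the relation between percentile and z.

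The cost in power is illustrative. It rests on assumed effects and variances, on baseline being used, and on ignoring clustering. It is large if the effect is confined to heavier children, modest if uniform, and close to nil without baseline.

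This is a minor point on one secondary outcome. The primary outcome, accurate maternal perception, uses percentiles only to classify children and is unaffected.

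**What to change.** - In the section on the intervention effect, replace BMI percentile as the dependent variable with the WHO BMI-for-age z-score, and name the baseline z-score as a covariate.
- Keep percentiles only for classifying weight status.
- In Outcome evaluation, name the same measure, so that the outcome as defined and the outcome as analysed agree.

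The cost is wording only. The z-score comes from the same weight, height, age and sex and the same WHO reference, and the protocol already collects data on all participants at baseline and after the intervention.

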**Methods/Design:**

The “Healthy Change” is a multicenter two-arm randomized trial in four centers. Three centers are in Mexican States (Nuevo Leon, Tamaulipas, and Zacatecas). The fourth center is in San Antonio, Texas, USA. A total of 360 mother-child pairs (90 pairs per center) are to be randomly and evenly allocated to either the intervention or the control group. Intervention group will receive four-session group obesity prevention education. Control group will receive a four-session personal and food hygiene education. The education is delivered by trained peer-mother promotoras. Data will be collected using questionnaires and focus groups. The primary outcome is a change in proportion of mothers with accurate MPCW. Secondary outcomes include change in maternal feeding styles and practices, maternal self-efficacy and actions for managing child excessive weight gain.

McNemar’s Test will be used to test the primary outcome. The GLM Univariate procedure will be used to determine intervention effects on secondary outcomes. The models will include the secondary outcome measures as the dependent variables, treatment condition (intervention/control) as the fixed factor, and confounding factors (e.g., mother’s education, children’s gender and age) as covariates. Sub-analyses will be performed to compare intervention effects on primary and secondary outcomes between the samples from Mexico and Texas, USA. Qualitative data will be analyzed through analysis of inductive content. A combined coding model will be developed and used to code transcripts using the NVivo software.

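### The stated model for the secondary outcomes does not name the outcome's baseline value as a covariate and leaves open whether the post score or the change is analysed

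*Protocol article*

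**What the plan says.** The model appears twice in the protocol article. Under Data analysis, Healthy change intervention effect: "The GLM Univariate procedure will be used to determine intervention effects on secondary outcomes". The outcome measures are the dependent variables, and the model terms are "treatment condition (intervention versus control) as the fixed factor, and confounding factors (e.g., mother’s education level, children’s gender and age) as covariates". The Abstract (Methods/Design) repeats it: "treatment condition (intervention/control) as the fixed factor, and confounding factors (e.g., mother’s education, children’s gender and age) as covariates". Neither place names the baseline value of the outcome.

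Three other statements bear on this:

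- Outcome evaluation: "Baseline and post-intervention data will be collected on all participants".
- Trial design: "At each site, two childcare centers are randomly assigned to either the intervention or the attention control group". There are four sites, and Childcare center recruitment and randomization allows a third centre at a site if recruitment falls short. That makes about four centres per arm.
- Abstract: "Secondary outcomes include change in maternal feeding styles and practices, maternal self-efficacy". Trial design and Outcome evaluation also word the secondary outcomes largely as change, increase, improvement or reduction. The analysis section speaks only of the outcome measures.

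Location enters the analysis only through a comparison of the Mexican and Texan samples.

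**The concern.** For a score measured twice, about four weeks apart, the first measurement is usually the best single predictor of the second. A model that adjusts for education, sex and age but not for that measurement leaves explainable variation in the error term.

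The small number of randomised units adds to this. With about four centres per arm, the arms can easily differ at baseline by chance, and part of any difference passes into the estimated intervention effect. The direction depends on whether the post score or the change is analysed, and the article does not settle which. A reader could not tell which way a given imbalance had pushed the result, and the choice could still be made after the data are seen.

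**Working it through.** **The plan's own figure.** The article's only sample-size figure is 37 pairs per research site per arm, for the primary outcome. It reproduces with proportions 50% and 70%, 80% power, unpooled variance, ICC 0.03, four clusters per arm and an assumed one-sided 5% level (the article states no alpha):

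- n = (1.645 + 0.842)² × (0.25 + 0.21) / 0.20² = 71.1 per arm before clustering.
- m = 71.1 × 0.97 / (4 - 71.1 × 0.03) = 36.9, so 37.

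The present point changes neither this figure nor the total of 360. The 37 serves below as the number of completers per centre, giving 4 × 37 = 148 per arm.

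**How large a chance imbalance is plausible?** Assume that the ICC of 0.03, stated for the primary outcome, also holds for the secondary scores.

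- Design effect = 1 + (37 - 1) × 0.03 = 2.08.
- SD of the baseline difference between arms = √(2 × 2.08 / 148) = 0.168 SD.
- P(|difference| > 0.2 SD): 0.2 / 0.168 = 1.19, so about 23% per outcome. With individual randomisation of the same numbers it would be √(2/148) = 0.116, 0.2 / 0.116 = 1.72, about 9%.

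**What baseline adjustment buys.** Let r be the baseline-to-post correlation, with equal SDs at both times and the same r within and between centres. The article gives no r, so a range is shown. Residual variance in units of the outcome variance is 1 for a post score, 2(1 - r) for a change score and 1 - r² with baseline as covariate. A baseline imbalance d carries over as r × d for a post score and (r - 1) × d for a change score; here d = 0.2 SD.

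| r | Change score 2(1 - r) | Adjusted 1 - r² | Cut vs post score | Cut vs change score | Carry-over, post | Carry-over, change |
|---|---|---|---|---|---|---|
| 0.5 | 1.00 | 0.75 | 25% | 25% | +0.10 SD | -0.10 SD |
| 0.7 | 0.60 | 0.51 | 49% | 15% | +0.14 SD | -0.06 SD |
| 0.9 | 0.20 | 0.19 | 81% | 5% | +0.18 SD | -0.02 SD |

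**Detectable difference** (80% power, two-sided 5% assumed, normal approximation, design effect held at 2.08): an unadjusted post score gives 2.80 × 0.168 = 0.470 SD. Multiplying by the square root of each factor:

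- r = 0.5: change score 0.470, adjusted 0.407.
- r = 0.7: change score 0.364, adjusted 0.335.
- r = 0.9: change score 0.210, adjusted 0.205.

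**Site.** If site explains a share f of the variance, leaving it out multiplies the standard error by 1/√(1 - f): 1.01 at f = 2% and 1.12 at f = 20%. In a centre-level analysis of eight centres, arm alone leaves 8 - 2 = 6 df, and arm plus site leaves 8 - 1 - 1 - 3 = 3 df. The two-sided 5% critical t rises from 2.45 to 3.18. To break even on interval width, site would have to explain about 1 - (2.45/3.18)² = 41% of the variance of the centre means.

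**The case against.** The strongest reply is that the covariate list is open: education, sex and age are given as examples. A reader might infer that baseline and site are excluded from the model. The text does not support that; it supports only that they are not named. This is a journal article, and a fuller plan that is not shown may complete the list. That reply stands as to wording. It does not remove the point, because the article does fix a concrete model twice, all its examples are demographic, and the dependent variable is left ambiguous.

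Second, the outcomes are worded largely as change, and GLM Univariate accepts a change score, or a baseline covariate, without difficulty. On the change-score reading baseline is already in use. A reader might take the 81% variance reduction at r = 0.9 as the expected gain for child BMI or fat percentage. It holds only against a raw post score; against a change score it is 5%. This objection stands, which is why both readings are shown. Adjustment is still the more efficient choice under either, and it removes the carry-over.

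Third, a reader might infer that leaving out site biases the results because centres are randomised within site. With 45 pairs planned per arm in every site, it does not. It can cost some precision, and including site in a centre-level analysis costs degrees of freedom. This objection also stands.

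Finally, feeding style is a four-category classification, to which the variance argument does not apply. These are also secondary outcomes of a study that calls itself a pilot.

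**Conclusion.** The point holds for the continuous secondary outcomes: the stated model does not name the baseline value and does not define the dependent variable. The gain from adjustment is 25% to 81% of residual variance if the post score was meant, and 25% down to 5% if the change was meant, for r from 0.5 to 0.9. A 0.2 SD imbalance, with roughly a 23% chance per outcome, would shift the estimate by +0.10 to +0.18 SD or by -0.10 to -0.02 SD respectively. These sizes rest on assumed correlations, on the primary outcome's ICC applying to the other scores, and on 37 completers in each of eight centres.

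The documents do not support saying that baseline is excluded, that the larger gains are certain, or that the missing site term causes bias. The primary analysis and the stated sample size are untouched. It is a worthwhile correction of moderate weight.

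**What to change.** For each continuous secondary outcome, state that the dependent variable is the post-intervention value, and name its own baseline value as a covariate beside arm and the listed covariates. Account for the childcare centre as the randomised cluster, and report the adjusted mean difference with its 95% confidence interval. With baseline in a linear model, the arm estimate is the same whether post score or change is the dependent variable, so the ambiguity disappears.

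The centre must be handled as well, because a baseline term does not deal with clustering. At a design effect of 2.08, a nominal two-sided 5% test that ignores it has a type I error of about 17% (1.96/√2.08 = 1.36, normal approximation).

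A site factor may be added to reflect randomisation within site. It is optional, given the fall from 6 to 3 df in a centre-level analysis, but the choice should be made before the data are analysed. Feeding style needs its own statement of method.

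The cost is a few lines of analysis text. No further data are needed, since baseline is already collected on every participant.

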## Methods

### Aims

This pilot study aims to develop and test the effects of the “Healthy Change” intervention on changing maternal perception of preschoolers’ weight status among Mexican mothers in México, and Hispanic mothers in San Antonio, Texas. Specific objectives are 1) To test the feasibility of “Healthy Change” intervention when implemented in a childcare setting; 2) To assess the effect of “Healthy Change” intervention on changing maternal perception of their preschoolers’ weight status; and 3) To assess the effect of the “Healthy Change” intervention on changing parenting style, maternal attitude, self-efficacy and practice toward raising healthy weight children.

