### Study setting

The study will be conducted in childcare settings, i.e., kindergarten classes in Mexico and Head Start Centers in Texas, USA.

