### Childcare center recruitment and randomization

Each research site will recruit a total of 90 pairs of preschoolers and their mothers with 45 pairs in the intervention and 45 pairs in the control group. Each research site initially recruits two childcare institutions with similar size and demographic profiles to participate in the study. The administrators of these centers are informed of the possibility of being assigned to either the intervention or the control group. Prior to participant recruitment, the two or three childcare institutions at each research center are randomly assigned to one of the two treatment groups using a random number table. In the event that an insufficient sample is recruited from the participating centers, a third center will be added to ensure adequate sample in the designated group.

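### The planned Mexico-versus-Texas comparison of intervention effects rests on one Texas site with a single childcare centre in at least one arm, so a country difference cannot be told apart from a difference between centres

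*Protocol article*

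**What the plan says.** In the protocol article, the Data analysis subsection on the intervention effect ends: "Sub-analyses will be performed to compare intervention effects on both primary and secondary outcomes between the samples from Mexico and Texas, USA". The abstract (Methods/Design) repeats this. The analyses named beside it are McNemar's test and a univariate GLM with treatment and mother and child covariates. No centre or site term is named.

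Trial design gives "four research sites, three in Mexico: a) Nuevo León, b) Tamaulipas, and c) Zacatecas, and one in San Antonio, Texas, USA", and says how treatment is assigned: "At each site, two childcare centers are randomly assigned to either the intervention or the attention control group". The section on childcare center recruitment and randomization adds one contingency: "In the event that an insufficient sample is recruited from the participating centers, a third center will be added to ensure adequate sample". It places that extra centre in the arm that needs it.

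The Aims describe the population as mothers "among Mexican mothers in México, and Hispanic mothers in San Antonio, Texas". Study setting gives "kindergarten classes in Mexico and Head Start Centers in Texas, USA".

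The sample size section works at centre level: "Assuming the intra-class correlation coefficient (ICC) of 0.03", and for a change "from 50 to 70% with 80% power, 37 mother-child pairs would be required per research center per arm".

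**The concern.** With one centre per arm, the Texas between-arm difference is also the difference between two particular Head Start centres. Deliverers and venue are tied to the centre as well. Promotoras must have a child enrolled there (Procedure to implement the intervention), and sessions are held in the mothers' own institution (Intervention). Texas data alone leave no degrees of freedom to judge how far two centres would differ without any intervention. By assuming a non-zero ICC, the plan itself expects such differences.

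Country is also carried by a single site and coincides with setting. Sessions are in Spanish in Mexico and in the mother's preferred language in Texas. Acculturation is measured only in Texas, so it cannot be used to adjust across countries.

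At stake is what the sub-analysis may be taken to show. A nominally significant contrast could reflect one unusual centre. A non-significant one could be taken as equal effects in both countries, although the design could miss very large differences. The Discussion looks ahead to a larger trial, and either misreading could affect how that trial is planned.

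**Working it through.** **Inputs.** ICC 0.03, 50% versus 70%, 80% power, 37 pairs per arm per site, 15% attrition and 45 enrolled (Sample size and statistical power); three Mexican sites, one Texan, two centres each (Trial design). Alpha and sidedness are not stated. I apply the ICC at childcare-centre level.

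**Reproducing the plan's 37.** With k = 4 centres per arm, m = n0(1 − ICC)/(k − n0 × ICC), where n0 is the unpooled two-proportion sample size.
- One-sided 5%: n0 = (1.645 + 0.842)² × (0.25 + 0.21)/0.20² = 71.1, so m = 71.1 × 0.97/(4 − 2.13) = 36.9, rounded up to 37. This matches.
- Two-sided 5%: n0 = 90.3, so m = 67.8, rounded up to 68. This does not match.
- Attrition: 37/0.85 = 43.5, so 44; the plan enrols 45. Total 45 × 2 × 4 = 360.

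The plan's figure is thus consistent with one centre per arm at each site.

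**Texas effect, m = 37.**
- Design effect = 1 + 36 × 0.03 = 2.08.
- SE = √(0.46/37 × 2.08) = 0.161; ignoring centres, √(0.46/37) = 0.112.
- 95% interval: about ±1.96 × 0.161 = ±32 points.
- The between-centre part is about √(0.03 × 0.46) = 0.117. Enrolling more mothers in the same two centres does not shrink it.

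**Mexico minus Texas.** Mexico averages three site differences, so the variance is the Texas variance × (1 + 1/3).
- SE = 0.161 × √(4/3) = 0.186; ignoring centres, 0.129.
- Detectable with 80% power, two-sided 5%: 2.80 × 0.186 = 0.52; ignoring centres, 0.36. With 45 per arm and centres included, 0.50.
- True type I error of a two-sided 5% test that ignores centres: 2 × [1 − Φ(1.96/√2.08)] = 0.17.

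**Assumed range of ICC, m = 37.** Contrast SE = 0.129 × √(design effect).

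| ICC | Design effect | Contrast SE | Detectable difference | Type I error if centres ignored |
|---|---|---|---|---|
| 0.01 | 1.36 | 0.150 | 42 points | 9% |
| 0.03 (plan) | 2.08 | 0.186 | 52 points | 17% |
| 0.05 | 2.80 | 0.215 | 60 points | 24% |
| 0.10 | 4.60 | 0.276 | 77 points | 36% |

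**Borrowing variance from Mexico.** Three Mexican site pairs give 2 degrees of freedom and a critical t of 4.30. With the contrast SE of 0.186, power is about 10% for a 20-point difference in effects and 24% for 40 points.

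**Third Texas centre, 45 pairs per arm.** Suppose the intervention arm is split over two centres of 22.5 pairs on average. Its design effect is 1 + 21.5 × 0.03 = 1.645, and the control arm's stays at 1 + 44 × 0.03 = 2.32. The variance is 0.25/45 × 2.32 + 0.21/45 × 1.645 = 0.0206, so the SE is 0.143, against 0.154 with two centres.

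**The case against.** The strongest reply is that this is a pilot, the country comparison is not one of its three objectives, and the text promises only sub-analyses. It names no p-value, threshold or attribution to culture, and how such an analysis is modelled and labelled could sit in a fuller document. A reader might infer that the protocol sets out to prove a national or cultural difference; it does not say so. What stands against this reply is that the comparison of effects is itself stated, and no later analysis plan can create replication within Texas.

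A reader might also infer that no statistical model could give a Mexico-Texas contrast. That is too strong. A model over all sites can borrow between-centre variance from Mexico. It then rests on an untestable assumption about Texas and has very little power, and country remains inseparable from one site and one setting.

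Nor are exactly two Texas centres certain, since a third may be added. One arm would still have a single centre, and the gain in precision is small.

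The figures use post-intervention proportions only. Baseline data are collected, and using them could lower the standard error. The documents give no correlation, so the gain is unknown. It would not remove the confounding.

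Low power alone is ordinary for a sub-analysis and would not justify a change. The case rests on the confounding and on error bars that are too narrow if centres are left out.

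**Conclusion.** The point holds for the country sub-analysis. As designed, the Texas effect cannot be separated from a difference between individual centres using Texas data alone, and a Mexico-Texas difference cannot be attributed to country. On the plan's own inputs the contrast has a standard error of about 19 points and a detectable difference of about 52 points, against a planned overall effect of 20. A two-sided 5% test without centres would reject a true null about 17% of the time (about 9% to 36% for an assumed ICC of 0.01 to 0.10).

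These sizes assume that the ICC applies at centre level and is known, that the variance is the same at all sites, and that baseline is not used. The two-sided 5% level is mine, since the article states none.

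It would go too far to conclude that the pooled four-site comparison fails for this reason. That comparison has four centres per arm. It needs an analysis that accounts for centres, but that is a separate matter.

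**What to change.** In the abstract and in the Data analysis subsection on the intervention effect:

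- Describe the Mexico-Texas comparison as descriptive and exploratory, with no test or p-value.
- Show the between-arm difference for each of the four sites side by side as point estimates. Every site starts with one centre per arm, so a site interval built only from variation among mothers would be too narrow in Mexico as well. Give intervals only if they include between-centre variance, taken from the stated ICC over a range or borrowed across sites, and label them as such.
- State that the Texas result rests on one site with a single centre in at least one arm and cannot be attributed to country.
- Keep inferential conclusions for the pooled four-site effect, analysed in a way that accounts for centres.

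This changes wording only and needs no new data. The cost is that a claim of a country difference in effect is given up.
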